### Recruitment

The participants will be recruited via distribution of flyers at the university psychotherapy outpatient clinic (Zentrum für Psychologische Psychotherapie) and at local psychotherapeutic and gynaecologist doctor’s offices in Greifswald and surroundings. Furthermore, we will search for participants via articles and announcements in the local newspaper. Telephone screenings assessing inclusion and exclusion criteria will be conducted with all potential participants, and study information will be provided. Eligible participants will be invited for baseline assessment.

### Methods: randomisation and blinding

#### Randomisation

Allocation of the participants to the experimental groups will be performed by a researcher not involved in the study. Participants will be randomly allocated in a 1:1 ratio to the two groups (anodal vs sham tDCS). Baseline performance in the n-back task will be used as strata (two performance strata; ≤87% correct and >87% correct in the n-back task). This 87% cut-off was empirically derived from prior studies using identical n-back paradigms,^59^ ensuring balanced distribution of high-performing and low-performing individuals across groups while maintaining sensitivity to detect stimulation and training effects at the group level. Randomisation blocks with varying block sizes will be generated for each of the two stimulation groups, using R software (https://www.R-project.org) and the blockrand package (http://CRAN.R-project.org/package=blockrand). Participants will then be allocated to the anodal or sham tDCS group based on the generated randomisation sequences within each block and stratum.

#### Blinding

As this is a double-blind trial, participants and investigators will be blinded regarding the stimulation condition. In the sham group, the current will be applied for 30 s to blind the participants to the intervention. In previous studies, sham tDCS has been shown to be a safe and valid method of blinding participants.^60^,^63^ At the end of the nine-session intervention, participants will be asked to state if they believe they received anodal or sham stimulation. As for the investigator blinding, a staff member who is not involved in this project will perform the randomisation according to the procedure described above and provide unidentifiable labels for the two stimulation protocols (anodal, sham) for the assessor. The assessor blinding will be ensured by using NIC software (https://www.neuroelectrics.com/), where the assessor will decide between ‘Protocol A’ and ‘Protocol B’ that corresponds to the participants ID number and will be able to apply the stimulation accordingly without knowledge of the respective stimulation condition.

### Methods: data collection, management and analysis

#### Data collection methods

Neuropsychological, behavioural, sleep data, as well as MRI data and blood samples will be collected from each participant. Study investigators will be thoroughly trained in administering the assessments. Additionally, participants will receive in-depth training on the handling of the Actigraph so that they can adequately and safely administer the sleep recording on their own. The questionnaires that are handed out to the participants will be explained by an investigator and will be accompanied by additional written instructions on how and when to complete the questionnaire. Time points and methods of data collection are shown in table 1. MRI data will be collected for individuals participating in the ‘add-on’ MRI study (optional) unless there are contraindications to MRI scanning.

**Table 1 T1:** Neuromod-PCSCI outcome measures

Time point	Measurement	Mode	Baseline	Pre	T1-T9 (3 weeks)	Post (3 days)	FU (1 month)
			∼3 hours	∼2 hours	∼1 hours	∼2 hours	∼2 hours
			V0	V1	V2–V10	V11	V12
Enrolment							
Eligibility screening		Paper	x				
Informed consent		Paper	x				
Neuropsychological screening	Demographic data	Paper	x				
	CTS^69^	Paper	x				
	AVLT^64^	Paper	x				
	Digit Span^48^	Paper	x				
	Stroop^65^	Paper	x				
	TMT A/B^66^	Paper	x				
	ROCF^67^	Paper	x				
Quality of life	PROMIS^51^	Paper		x		x	x
	EORTC QLQ C30^71^	Paper		x		x	x
	EORTC BR23^71^	Paper		x		x	x
	FACT Cog^72^	Paper		x		x	x
Sleep data	Epworth Sleepiness Scale^53^	Paper	x				
	Pittsburgh Sleep Quality Index^73^	Paper		x		x	
	Morningness-Eveningness-Questionnaire^54^	Paper	x				
	Actigraph	Device		x		x	
Intervention					⟷		
Training task	Letter updating^49 92^ 93	Tablet-Computer	x	x	x	x	x
Brain stimulation	tDCS (anodal vs sham)	Device			x		
Questionnaires	Self-reported well-being	Paper		x	x	x	x
	PANAS^93^	Paper			x		
	Adverse Events Questionnaire^34^*	Paper			x		
Additional assessments							
Untrained tasks	n-back (primary outcome)^48^	Computer		x		x	x
	Virtual reality task^50^	Computer		x		x	x
Physical measures	MRI, optional			x		x	
	Blood draw		Once at any of these sessions				
Feasibility	Adherence rates	Paper			x	x	

All measures were acquired on site, except for screening which was done via telephone.

* Assessed only at the end of each training week (V4, V7 and 10).

AVLT, German version of the auditory verbal learning test; CTS, childhood trauma screener; EORTC QLQ C3/BR23, European Organization for Research and Treatment of Cancer, Quality of Life Questionnaire (QLQ C30), supplemented with the extension regarding breast cancer specific quality of life (BR23); FU, follow-up assessment; PANAS, positive and negative affect schedule; PROMIS, patient reported outcomes measurement system; ROCF, Rey-Osterrieth complex figure test; tDCS, transcranial direct current stimulation; TMT A/B, trail making test A/B; T1-T9, training 1-9; V0-V12, visits 0-12.

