### Exploratory analyses

Exploratory analyses will be conducted for more detailed outcomes of the training task (eg, outcomes dependent on list length in the LU task). Additionally, education, baseline cognitive ability or neuropsychological status, as well as sociodemographic and clinical characteristics, will be analysed to identify potential predictors of training task performance and response to the intervention. Moreover, learning-relevant polymorphisms as well as (neuro-)inflammatory markers in collected blood samples will be analysed to examine mechanisms underlying PCCI pathology and their link to beneficial training gains induced by the intervention.

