### Participant timeline

Individuals will participate in 13 visits and two optional MRI sessions, taking place at the University Medicine Greifswald. After inclusion at baseline visit (V0), participants will attend the pre-assessment visit (V1, Friday) before starting the nine training visits during three consecutive weeks on 3 days a week (V2–V10). The cognitive training intervention will take place on Monday (M), Wednesday (W) and Friday (F). After the training, a post-assessment (V11, Monday) will be conducted and 4 weeks later a follow-up visit (V12) will be administered. MRI will be acquired before pre-assessment (V1) and at post-assessment (V13). Figure 2 provides a concise overview of this participant timeline.

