### Sample size

Power calculation is based on recent studies using multisession application of cognitive training compared with a control training on immediate performance in the trained task (primary outcome).^55^,^57^ Based on these data, we estimated an effect size of 0.7 (Cohen’s d). To demonstrate an effect in the primary outcome between cognitive training groups and control (% correct in the n-back task for the anodal vs sham stimulation group) with an independent t-test using a two-sided significance level of α=0.1 and a power of at least 80 %, 52 participants (26 for target intervention group, 26 for control intervention group) need to be included. This conservative approach using a t-test was chosen for sample size estimation, even though we intend to analyse the primary outcome conducting an analysis of covariance (ANCOVA) model.^58^ This monocentric clinical trial will serve to calculate sample size for a subsequent multicentre clinical trial. Sample size estimation was conducted using R software (http://www.R-project.org) and the pwr package (https://cran.r-project.org/package=pwr). To account for approximately a 13% drop-out during the intervention phase, the total number to recruit is 60 (30/group).

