#### Blood draw

At one of the sessions, a peripheral blood sample for conducting genetic analyses will be collected, preprocessed and stored at the Neuroimmunology Lab of University Medicine Greifswald, using cryo-preservation method. 2.5 mL of EDTA blood will be collected for analysing genetic polymorphisms relevant for learning processes such as ApoE4 or BDNF. In addition, 5 mL of peripheral blood will be withdrawn to gain 2.5 mL of serum for biomarker analyses to gain information on (neuro-)inflammatory processes. We will quantify NAA/Cho, anti-NMDA-antibodies and VILIP-1, CCL2 (MCP-1), sTREM-2, BDNF, TGF-β1, VEGF, IL-6, sTREM-1, β-NGF, IL-18, TNF-α, sRAGE, CX3CL1 (Fractalkine), IL-1b and IL-10. Biomarker analyses will be performed at the Department of Neurology, Greifswald. Here, pseudonymised blood samples will be stored at −80°C until analysis. Rest material will be stored for up to 10 years. Analyses of anti-neural-antibodies will be performed at Labour Krone GbR in Bad Salzulfen, Germany. Genetic analyses will be performed at the Institute of Pharmacology at the University Medicine Greifswald.

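### The single blood draw has no fixed visit, so exploratory links between serum markers and training gains may mix pre-existing status with response to the intervention

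*Protocol article*

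**What the plan says.** All places are in the protocol article.

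- **Timing.** Table 1 (Data collection methods) gives the blood draw as "Once at any of these sessions". The Blood draw section says "At one of the sessions, a peripheral blood sample for conducting genetic analyses will be collected". Neither limits the draw to visits before stimulation, and no second sample is planned.
- **Content.** The EDTA part is for "analysing genetic polymorphisms relevant for learning processes such as ApoE4 or BDNF". For the serum part, "5 mL of peripheral blood will be withdrawn to gain 2.5 mL of serum for biomarker analyses to gain information on (neuro-)inflammatory processes". The marker list includes IL-6, TNF-α, IL-1b, IL-10, IL-18 and BDNF.
- **Use.** The Exploratory analyses section plans to use the polymorphisms and the (neuro-)inflammatory markers to study how PCCI arises and "their link to beneficial training gains induced by the intervention".
- **Schedule.** The Participant timeline states "Individuals will participate in 13 visits and two optional MRI sessions". V0 is baseline, V1 pre-assessment, V11 post-assessment and V12 follow-up. V2 to V10 are the "nine training visits during three consecutive weeks on 3 days a week", and stimulation is given at each of them.

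**The concern.** A free choice of visit suits genotype. It does not suit serum proteins, which can vary over weeks and could respond to three weeks of training with or without active stimulation. Under the rule as written, one woman's value may describe her state before the intervention, another's her state midway through it, and a third's her state a month after it ended.

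Both planned uses suffer. For the mechanisms of PCCI, mixed timing adds variation unrelated to the condition. For training gains, a late value may be a result of the intervention, or of the gain itself, and not something that preceded it. One draw per woman leaves no within-person contrast to tell these apart, and no later analysis can recover a baseline value that was never sampled.

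The trial is meant to guide later confirmatory trials (end of Introduction). An association read as prior biological status, when it is partly response, could be carried forward as a selection marker.

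**Working it through.** **1. Count of visits.** From the Participant timeline: V0 (1) + V1 (1) + V2–V10 (9) + V11 (1) + V12 (1) = 13, which agrees with the stated 13.

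- Wholly before the first stimulation: V0 and V1, 2 of 13.
- Ambiguous: V2, 1 of 13. A draw there may come before or after the stimulator is started.
- Certainly after the first stimulation: V3–V12, 10 of 13.

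**2. Position of randomisation.** The strata use n-back performance, and Table 1 first schedules the n-back at V1. Allocation by stratum therefore follows that test and precedes V2. Any sample taken after the first stimulation is thus a post-randomisation value.

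**3. What even spreading would imply.** The document gives no distribution of draw visits. Assume, for scale only, that draws fall evenly over the 13 visits among the 52 participants of the Sample size section:

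- V0 and V1 only: 52 × 2/13 = 8 women (15%) with a pre-stimulation value.
- Adding V2, if every V2 draw came first: 52 × 3/13 = 12 women (23%).

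Actual practice may cluster early or late; these figures do not describe it.

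**4. Whether the document fixes the size of a distortion.** Let f be the share of late draws and s the marker shift in SD units. Take a marker unrelated to gain before stimulation. Use the planning difference ("we estimated an effect size of 0.7") for gain, with within-arm SD 1. Both f (0.5 to 10/13) and s (0.3 to 0.5) are assumptions.

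*Mechanism A: the shift is proportional to each woman's gain.* Within the anodal arm,

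r = s·f / √[1 + s²(1.49·f − 0.49·f²)]

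- s = 0.3, f = 0.5: 0.150 / √1.056 = 0.15
- s = 0.5, f = 10/13: 0.385 / √1.214 = 0.35

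*Mechanism B: a constant shift in the anodal arm only.* Pooled over arms,

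r = 0.7·0.25·s·f / √{1.1225 · [1 + s²·(f/2)(1 − f/2)]}

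- s = 0.3, f = 0.5: 0.0263 / 1.068 = 0.025
- s = 0.5, f = 10/13: 0.0673 / 1.090 = 0.062

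With all draws before stimulation (f = 0), r = 0 under both. The answer therefore runs from negligible to moderate according to a mechanism and inputs that the document does not supply. The arithmetic shows that the ambiguity can matter; it does not estimate how much it does.

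**5. Comparison within the protocol.** MRI, which also serves to study neural predictors and correlates, is fixed before the intervention and at post-assessment. The serum sample has no such anchor.

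**The case against.** **A stronger claim might be inferred:** that the plan misuses these markers as baseline predictors or moderators, and that a false group-by-marker interaction will follow. The text does not support this. The Exploratory analyses section names its candidate predictors (education, baseline cognition or neuropsychological status, sociodemographic and clinical characteristics) and treats the blood markers in a separate sentence. That sentence speaks only of mechanisms and a link to gains. No marker-by-group interaction is planned. What stands is the narrower point: even a link is hard to interpret when the marker may precede or follow the gain.

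**Nor are the markers unusable as a set.** Samples from V0 or V1, and from V2 if drawn before stimulation began, are valid pre-stimulation values. The document does not say that the sampling visit goes unrecorded.

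**A difference between arms does not follow automatically.** Both arms complete the same nine training sessions. A shift due to training or time would occur in both arms; only one specific to active stimulation would separate them. This limits claims about between-arm imbalance, but not the ambiguity of a marker-gain association within an arm.

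**The table is damaged in extraction,** so the span of its merged cell is uncertain. The Blood draw section is equally unrestricted, so the reading holds, although the visit count comes from the timeline and not from the table cell.

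**Handling of late samples may sit in the SAP or a laboratory procedure.** That is fair, and its absence here is no fault. The timing rule itself, however, is stated in the article and is poorly suited to one of its two uses.

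**Conclusion.** The concern holds in a limited form. The protocol fixes a timing rule that suits genotyping and applies it to serum markers that vary over time. Following it as written can mix values from before, during and after the intervention. An exploratory marker-gain association could then not be separated into pre-existing status and response.

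Severity is low. Genotype, the primary n-back outcome, the secondary outcomes and the sample size are unaffected. The size of any bias is unknown from the document, because it depends on when draws were actually taken and on whether the markers move with training or stimulation. The conclusion assumes only that these serum markers may change during the study and that some draws occur after the first stimulation. If in practice all draws were made at V0 or V1, the problem would not arise.

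**What to change.** For remaining participants, take the whole draw, EDTA and serum together, at V0 or V1, before the first stimulation. Keeping the two tubes together avoids a second venepuncture.

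For women already sampled, use the recorded sampling visit to restrict serum marker-gain analyses to pre-stimulation samples. Count a V2 sample only where the record shows that it preceded the start of stimulation. Report later samples descriptively, by visit. Genetic analyses can use every sample.

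The cost is a scheduling instruction and a sentence in the analysis plan, with no added procedure. The downside is fewer usable serum samples among women sampled late. With enrolment open since November 2021 and the study due to end in June 2026, that loss may be appreciable; the document does not say how many draws are already done.

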#### Neuropsychological assessment

Neuropsychological tests at baseline visit (V0) comprise paper-pencil as well as computer-based assessments. Performance in several cognitive domains will be tested with the auditory verbal learning test,^48 64^ the Digit Span,^48^ the Stroop test,^48 65^ the Trail Making Test A/B,^66^ and the Rey-Osterrieth Complex Figure Test.^67^

Trained and untrained tasks include paper-pencil and computer-based assessments. Detailed description of the training task is provided in the interventions section. At pre, post and follow-up sessions (V1, V11 and V12), the untrained tasks will be administered: Participants will perform a numeric n-back task (1 and 2 back) and a VR navigation task.^50^ The n-back (1 and 2 back) task will be administered as an untrained task to assess working memory function (18 trials total, 9 trials 1-back and 9 trials 2-back with 10 items each, presentation duration 1500 ms, ISI 2500 ms). The participants will have to state for a sequence of numerical digits presented one after the other, if the stimulus that is presented currently is the same stimulus as ‘n’-steps back. The participants will answer via a keypress, left arrow key for ‘yes’ if the stimuli match and right arrow key for ‘no’ if the stimuli differ. This task requires that different brain functions are coordinated effectively including updating, discrimination and matching of the stimuli and decision making.^48 68^ The VR task^50^ will be administered as an untrained task. Here, during encoding, participants will be instructed to memorise a route with several targets (eg, butcher, doctor’s office and grocery store); during subsequent recall, the participants will be asked to navigate the shortest route to given targets.

#### Psychological assessment

A variety of questionnaires will be administered over the course of the study. At the baseline visit (V0), the participants will be screened for childhood maltreatment and various mental disorders via the CTS^69^ and the DIPS.^70^ The CTS is a 5-item questionnaire regarding experiences of neglect and abuse in childhood and adolescence. The DIPS is an established diagnostic interview which helps to thoroughly explore different possible mental diagnoses. It guides the interviewer, covering the different aspects of each disorder, the degree of symptom expression, and subsequently aids in classifying the possible mental disorders according to DSM-5.

At pre, post and follow-up assessments, the following Quality of Life Questionnaires will be administered:

Patient Reported Outcomes Measure System (PROMIS, https://promis-germany.de/) to assess physical, mental and social healthEORTC QLQ C30,^71^ to measure QoL of cancer patientsEORTC BR23, which is a module of the EORTC QLQ C30 and focuses on the mental and physical health of breast cancer patientsFACT Cog,^72^ to gain additional insights on perceived cognitive impairments in cancer patients with chemotherapy-induced cognitive problems

Simultaneously with the collection of sleep data through actigraphy, the participants will be asked to fill in three questionnaires regarding their sleep quality and rhythm. The Morningness-Eveningness Questionnaire^54^ and the Epworth Sleepiness Scale^53^ will be administered at Baseline assessment. The Pittsburgh Sleep Index^73^ will be administered both at pre-assessment and post-assessment, assessing day-time sleepiness, quality of sleep and the sleep rhythm of the participants in the last month/weeks.

#### Magnetic resonance imaging

MRI will be acquired at the Baltic Imaging Center (Center for Diagnostic Radiology and Neuroradiology, Universitätsmedizin Greifswald) with a 3-Tesla scanner (Siemens Verio) using a 32-channel head coil, prior to the training intervention and at post-intervention. A T1-weighted 3D sequence, a 3D FLAIR, diffusion tensor imaging (DTI) and a resting-state fMRI sequence will be recorded. Additional T1-weighted and T2-weighted structural images will be acquired with parameters optimised for computational modelling to calculate electric field distributions (simnibs.org).^74 75^ Seed-based resting-state functional connectivity within and between large-scale task-relevant networks (eg, frontoparietal and default mode network) will be performed^55 76 77^ using the CONN toolbox (www.nitrc.org/projects/conn).^78^ White-matter pathways will be reconstructed from diffusion-weighted images using the TRACULA pipeline^79^ in Freesurfer (http://surfer.nmr.mgh.harvard.edu/), in order to extract tract fractional anisotropy and mean diffusivity.^80^,^83^ Changes in FA and MD on whole-brain level will be analysed using FSL’s tract-based spatial statistics (TBSS, www.fmrib.ox.ac.uk/fsl).^84 85^ MD in grey matter will also be explored for examination of intervention-induced microstructural grey matter change.^86^ Segmentation on high-resolution T1 scans will be performed to assess the volume of cortical and subcortical grey matter^49 87^ using the computational anatomy toolbox (CAT12, http://www.neuro.unijena.de/cat/) and Freesurfer (http://surfer.nmr.mgh.harvard.edu/).

#### Blood draw

At one of the sessions, a peripheral blood sample for conducting genetic analyses will be collected, preprocessed and stored at the Neuroimmunology Lab of University Medicine Greifswald, using cryo-preservation method. 2.5 mL of EDTA blood will be collected for analysing genetic polymorphisms relevant for learning processes such as ApoE4 or BDNF. In addition, 5 mL of peripheral blood will be withdrawn to gain 2.5 mL of serum for biomarker analyses to gain information on (neuro-)inflammatory processes. We will quantify NAA/Cho, anti-NMDA-antibodies and VILIP-1, CCL2 (MCP-1), sTREM-2, BDNF, TGF-β1, VEGF, IL-6, sTREM-1, β-NGF, IL-18, TNF-α, sRAGE, CX3CL1 (Fractalkine), IL-1b and IL-10. Biomarker analyses will be performed at the Department of Neurology, Greifswald. Here, pseudonymised blood samples will be stored at −80°C until analysis. Rest material will be stored for up to 10 years. Analyses of anti-neural-antibodies will be performed at Labour Krone GbR in Bad Salzulfen, Germany. Genetic analyses will be performed at the Institute of Pharmacology at the University Medicine Greifswald.

